### Data gathering

Data are being collected for patients in the intervention and the control group in identical ways. QoL and "cost questionnaires" are sent every three months (after each follow-up appointment) by the patients to the trial centre up to 24 months postoperatively. These questionnaires are optically readable, data being consecutively collected in a trial database.

SCEs are registered via hospital chart review at 24 months postoperatively. This follow-up period will allow identification of most SCEs, since tumour recurrence typically occurs within two years of surgery [11].

The study has been approved by the Norwegian Data Inspectorate. All data will be handled with strict confidentiality, and study reports or presentations will maintain the anonymity of patients, surgeons, GPs and hospitals. Data collection will be complete by the end of 2010.

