### Intervention

Patients are randomized to follow-up either by their GP (intervention) or at the surgical outpatient clinic. All patients will receive their first postoperative check-up at the hospital which performed the surgery (baseline, 1 month). A clinical examination will then be performed and information about the histology and the results of the surgery will be provided. If the patient gives informed consent, randomization is performed. Patients randomized to GP follow-up are referred to their GP. This referral contains information about the surgery and any complications, Dukes's staging, guidelines for follow-up and behavioural strategy in the case of a SCE.

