#### QOL questionnaires

The EQ-5D and EORTC-QLQ C30 questionnaires for the two-year follow-up period (at 1, 3, 6, 9, 12, 15, 18, 21, 24 month follow-up) are given to the patient at baseline examination.

Economic evaluation questionnaire: A questionnaire has been developed to enable calculation of costs related to patient examinations. This questionnaire is incorporated in the QOL questionnaire, and patients are requested to fill out the questionnaire at 1, 3 6, 9, 12, 15, 18, 21 and 24 months postoperatively. The cost elements will include patient- and family-related costs due to outpatient visits, GP visits, laboratory tests, radiographs/ultrasound, examinations due to suspected relapse, treatment of relapse, travelling, production losses, co-payments and other patient expenses.

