### Outcome measures

#### Primary outcome (measured at 1, 3, 6,9,12,15,18,21 and 24 months)

#### Quality of life

EQ-5D is a standardized generic instrument for use as a measure of health outcome. Applicable to a wide range of health conditions and treatments, it provides a simple descriptive profile and a single index value for health status. EQ-5D measures five dimensions of health-related quality of life (HRQOL): mobility, self-care, usual activities, pain/discomfort and anxiety/depression. EQ Visual Analogue Scale: The EQ VAS records the respondent's self-rated health status on a vertically graduated (0–100) visual analogue scale [13]. Quality of life assessment based upon the European Organization for Research and Treatment of Cancer Quality of Life questionnaire (EORTC QLQ C-30); EORTC QLQ C-30 incorporates nine multi-item scales: five functional scales (physical, role, cognitive, emotional and social); three symptom scales (fatigue, pain, nausea/vomiting); and a global health status/QOL scale. Six single-item scales are also included (dyspnoea, insomnia, appetite loss, constipation, diarrhoea and financial difficulties) [14].

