#### Economic analysis

A cost-effectiveness analysis will be performed alongside the randomized controlled trial. A Markov model will be employed. If the trial reveals no difference in health outcomes or quality of life of the patients, a cost-minimization analysis will be carried out. If we reveal a difference in quality of life between the two groups, we will implement a cost-utility analysis. The economic evaluation will have a health care and societal perspective. Resources used in both treatment arms will be registered prospectively based on reports by the patients and on the hospital patient records. Costs related to consultations at the primary and secondary care level, both at baseline and up to 24 months after randomization, including direct medical costs, indirect costs (production losses), travel costs and patient-/family-related costs will be registered. Quality of life measurements will be collected both at baseline and at several time points during the intervention. A 3% discount rate will be used to discount future costs and benefits. The cost elements will include costs related to outpatient visits, GP visits, laboratory tests, radiographs/ultrasound, examinations due to suspected relapse, treatment of relapse, travelling/transportation, production losses, co-payments and other patient/family expenses. The net costs and outcomes of the two treatment options will be compared and presented as incremental cost-effectiveness ratios.

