### Randomization

Randomization will be done at the 1-month check-up (baseline) after the patients have given informed consent. The randomization service is web-based and managed by the Norwegian University of Science and Technology. Patients are stratified according to the Dukes's staging and whether they have a stoma. Patients allocated to general practice follow-up may be referred back to surgical clinics at any point in the study; similarly, patients in the surgeon-led follow-up group are free to consult their GP at any time during the study.

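### As described, the month-1 baseline quality-of-life form can be completed after the patient already knows the allocation

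*Protocol article*

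**What the plan says.** The Intervention section of the Protocol article defines the baseline visit: "All patients will receive their first postoperative check-up at the hospital which performed the surgery (baseline, 1 month"). After the examination and the information on histology and surgery, "If the patient gives informed consent, randomization is performed". The Randomization section agrees: "Randomization will be done at the 1-month check-up (baseline) after the patients have given informed consent". Patients assigned to GP follow-up are then referred to their GP, so the allocation is open to them.

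The QOL questionnaires section lists the EQ-5D and QLQ-C30 forms "at 1, 3, 6, 9, 12, 15, 18, 21, 24 month follow-up" and says that they "are given to the patient at baseline examination". The cost questions are built into the same forms. The Data gathering section gives the return route: forms are sent in every three months, "after each follow-up appointment) by the patients to the trial centre up to 24 months postoperatively".

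The Economic analysis section treats baseline as a measurement in its own right: "Quality of life measurements will be collected both at baseline and at several time points during the intervention". The heading under Outcome measures nevertheless reads "Primary outcome (measured at 1, 3, 6,9,12,15,18,21 and 24 months"), which places month 1 among the primary-outcome times.

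**The concern.** Consent, randomisation and the hand-out of the month-1 form fall at one visit, and the form is described as something the patient sends in later. The patient cannot be blinded and the outcome is self-reported. Relief or disappointment at being assigned to the GP or to the surgical clinic could therefore enter the value that is meant to describe the patient before allocation.

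A baseline shifted in this way differs between the arms because of randomisation. Any analysis that subtracts it or adjusts for it carries the shift into the estimated effect with the opposite sign. If patients assigned to the GP score lower at month 1 out of disappointment, their later improvement looks larger, which favours the trial's hypothesis for the GP arm. If they score higher out of relief, a true benefit is understated. Analysis cannot separate clean from contaminated forms afterwards unless the time of completion was recorded.

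A second, smaller matter is that month 1 is named both as baseline and as a primary-outcome time. All patients have that check-up at the operating hospital, so there is no contrast in follow-up to measure there.

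**Working it through.** **Order of events.** The plan gives no figure for this point, so the first step is to set the sections side by side.

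1. Intervention and Randomization: the order is check-up, information, consent, randomisation, all at month 1. No questionnaire step is placed between consent and randomisation.
2. QOL questionnaires: the full set, including the month-1 form, is handed out at that examination. Whether this is before or after randomisation is not said.
3. Data gathering: the patient sends forms in after appointments. No separate route, such as collection in clinic, is given for the month-1 form.
4. Intervention: the referral to the GP reveals the allocation.

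Together these permit a month-1 form completed after allocation, and no section prevents it. They do not establish that it happens.

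**Which analyses would be affected.** Let b be the difference between the arms (GP minus control) at month 1 caused by knowing the allocation, r the slope of follow-up score on baseline score, and D the true follow-up difference.

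- Follow-up scores alone: estimate = D
- Baseline-adjusted: estimate = D − r × b
- Change from baseline: estimate = D − b

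**Illustration only.** D = 10 Global QoL units is the target in the Sample size section. The values of b (−5 to +5 units) and r (0.3 to 0.7) are assumptions with no source in the document.

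| b | Follow-up only | Adjusted, r = 0.5 | Change score |
|---|---|---|---|
| −5 | 10 | 10 + 2.5 = 12.5 | 10 + 5 = 15 |
| −2 | 10 | 10 + 1 = 11 | 10 + 2 = 12 |
| +2 | 10 | 10 − 1 = 9 | 10 − 2 = 8 |
| +5 | 10 | 10 − 2.5 = 7.5 | 10 − 5 = 5 |

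For b = +5, the adjusted estimate is 10 − 0.3 × 5 = 8.5 at r = 0.3 and 10 − 0.7 × 5 = 6.5 at r = 0.7. The table shows direction and mechanism; it does not estimate the bias in this trial.

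**The case against.** The strongest reply is that the article does not fix the order within the visit. A form filled in before the consultation can still be posted after it, because the Data gathering section describes sending, not completing. Its three-monthly rhythm fits months 3 to 24 better than the month-1 form. The order of steps at a single visit is also a detail that a condensed article may leave to the full protocol or site instructions.

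Much of this stands. A reader might infer that the month-1 form is in fact completed after allocation. The documents do not support that; they support only that it can be.

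A reader might also attach a size to the problem. Assumed reactions of 2 to 5 units give a bias of 1 unit (0.5 × 2, adjusted) to 5 units (change score), or 10% to 50% of the 10-unit target. Averaging nine equally weighted visits with month 1 included would dilute the effect by 1/9, or 11%. Neither figure is a finding about this trial. The Analysis section promises mean differences and covariate adjustment, but names no change score, no adjustment for baseline quality of life and no average over visits. The reaction size is assumed. The two figures also belong to different analyses, since a month-1 value used for adjustment would not normally be averaged as an outcome as well. The listing of month 1 under Outcome measures may be no more than a measurement schedule.

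What the reply does not remove is that the article does describe the hand-out, the randomisation and the return route, and that this described procedure leaves the baseline open to contamination. That is a matter of trial conduct, not an omitted analysis detail.

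**Conclusion.** The point holds as a weakness in the described procedure. The baseline of an open trial with a self-reported primary outcome is not protected from knowledge of the allocation. Whether contamination occurs is unknown, and its size cannot be derived from the document: it depends on how patients react and on whether the analysis uses the month-1 value. An unadjusted comparison of scores from month 3 onward is not affected, and the sample size does not change. The double role of month 1 as baseline and primary-outcome time is a lesser inconsistency that the same correction resolves. The matter should be corrected because the remedy is nearly free and the damage could not be undone at analysis.

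**What to change.** State in the protocol and on the randomisation form that the month-1 EQ-5D, QLQ-C30 and cost forms are completed and collected in clinic after consent and before the web randomisation is opened. Record the date and time of completion. Hand out only the forms for month 3 onward to take home.

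Use month 1 as baseline only, and start primary-outcome comparisons at month 3.

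For patients already enrolled, flag month-1 forms completed after allocation, or whose timing cannot be recovered. Keep these patients in the analysis, and add a sensitivity analysis without baseline adjustment.

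The cost is a few minutes at a visit that already takes place, plus a short addition to the protocol and the randomisation form.

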### Analysis

We will use the intention-to-treat principle when analysing data. Furthermore, we will employ Fayers guidelines to handle missing data [18]. Treatment arms will be compared with respect to potential covariates using continuous and categorical univariable analyses. These will include variables relating to patients (age, sex, comorbidities, cost), treatment (surgical resection, surgical complications, adjuvant therapy), tumour (Dukes's Stage), hospital surgical outpatient clinic (cost, patient satisfaction, QoL), GP practice (cost, patient satisfaction, QoL). The cost elements will include costs related to outpatient visits, GP visits, laboratory tests, radiographs/ultrasound, and examinations due to suspected relapse, treatment of relapse, travelling/transportation, production losses, co-payments and other patient expenses. The net costs and outcomes of the two treatment options will be compared and presented as cost-effectiveness ratios. If the trial reveals no difference in health outcomes or quality of life for the patients, a cost-minimization analysis will be carried out. If we find a difference in quality of life or overall survival rates between the two groups, we will use a cost-utility approach. The economic evaluation will have a societal and health care perspective.

The method of analysis, including adjusting for covariates will comply with the CONSORT statement [19]. The results will be expressed as odds ratios for binary outcomes, hazard ratios for time- to-event outcomes or mean differences for continuous outcomes with corresponding standard errors, 95% confidence intervals, and associated p-values. P-values will be reported to three decimal places with p-values less than 0.001 reported as p < 0.001. For all tests we will use alpha = 0.05 level of significance.

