### Sample size

Sample size calculations are according to Campbell's guidelines [15]

Alpha and beta were set at 0.05 and 0.2 respectively and tests were two-sided. We hypothesize that patients followed up by their GP will have a minor to moderate increase in the Global QoL scores (EORTOC-QLQ C30). This moderate effect size equals an increase of 10 units on the Global QOL [16]. Patients with colon cancer (local disease) show a standard deviation of approximately 20 (global QOL) [16]. Allowing for a dropout rate of 20%, to detect this difference with confidence we required a total sample size of 170 patients. Sample size calculations based upon EQ-5D showed similar results [17].

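### The list of potential covariates mixes outcomes and post-randomisation items with baseline variables, and names neither the 1-month QoL value nor stoma

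*Protocol article*

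**What the plan says.** All references are to the protocol article.

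- **Analysis.** "Treatment arms will be compared with respect to potential covariates using continuous and categorical univariable analyses". The variables then named are patient factors (age, sex, comorbidities, cost), treatment factors (resection, complications, adjuvant therapy), Dukes's stage, and a set of items for each follow-up setting. For the GP setting the entry reads "GP practice (cost, patient satisfaction, QoL", and the outpatient clinic has the same three items. Later in the section, the method of analysis, covariate adjustment included, is said to follow the CONSORT statement.
- **Primary objective.** QoL and costs are what the trial compares between the arms.
- **Randomization.** Allocation takes place at the 1-month check-up, which is also baseline. "Patients are stratified according to the Dukes's staging and whether they have a stoma".
- **Economic analysis.** "Quality of life measurements will be collected both at baseline and at several time points during the intervention". The section on QoL questionnaires confirms a 1-month assessment with both EQ-5D and EORTC QLQ-C30.

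**The concern.** The two setting labels in the covariate list are in effect the two arms. Satisfaction with follow-up in a setting, its cost, and QoL during it all arise after allocation, and cost and QoL are themselves outcomes. Adjusting a treatment comparison for a variable that the treatment can change removes part of the effect, or creates an effect where there is none. The same section provides for adjustment and states no other covariate set, so an analyst who takes the list at face value could do this.

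The consequence would reach beyond QoL. The choice between cost-minimisation and cost-utility analysis depends on whether a QoL difference is found, so a distorted QoL estimate could change the type of economic evaluation as well.

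The list also names Dukes's stage but not the other stratification factor, and QoL appears in it only under the follow-up settings, not as a 1-month value. That affects precision, not bias.

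**Working it through.** **Inputs from the Sample size section.** "Alpha and beta were set at 0.05 and 0.2 respectively and tests were two-sided"; "This moderate effect size equals an increase of 10 units on the Global QOL"; patients with local colon cancer "show a standard deviation of approximately 20 (global QOL"); "Allowing for a dropout rate of 20%, to detect this difference with confidence we required a total sample size of 170 patients". Equal allocation is assumed, because no ratio is stated.

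**The plan's own figure.** The normal approximation gives n per arm = 2 × (1.96 + 0.84)² × 20² / 10² = 63 after rounding up, so 126 in total and 126/0.8 = 158 with dropout. The t-test gives 64 per arm, 128 in total, 160 with dropout. Dividing 64 by a rank-test efficiency of 0.955 gives 68 per arm, 136 in total, and 136/0.8 = 170. This matches the stated total, although the article does not say that this method was used. Working back, 170 × 0.8 = 136 evaluable patients, or 68 per arm. The covariate point does not depend on how 170 was reached.

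**1. Leaving out baseline QoL.** With correlation ρ between the 1-month and follow-up values, the adjusted SD is 20 × √(1 − ρ²), and power ≈ Φ(10 / (SD × √(2/68)) − 1.96). The documents give no ρ, so the range 0.3 to 0.7 is an assumption.

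| ρ | SD | Power, normal approximation | Power, t-test |
|---|---|---|---|
| unadjusted | 20.00 | 83.0% | 82.5% |
| 0.3 | 19.08 | 86.4% | 85.9% |
| 0.5 | 17.32 | 92.0% | 91.7% |
| 0.6 | 16.00 | 95.4% | 95.1% |
| 0.7 | 14.28 | 98.3% | 98.2% |

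At ρ = 0.5 the residual variance falls by 25%, which is worth 1/(1 − 0.25) = 1.33 times the patients.

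**2. Adjusting for a post-randomisation item.** Suppose that the arm shifts satisfaction by d SD and that satisfaction correlates r with QoL within arms. The adjusted difference then has expectation (true difference) − 20 × r × d. Both d and r are assumptions. Simulation with 136 patients and 4,000 replicates per row gave:

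| d | r | True 10: expected estimate | True 10: power | True 0: expected estimate | True 0: false-positive rate |
|---|---|---|---|---|---|
| 0.3 | 0.3 | 8.2 | 69% | −1.8 | 8% |
| 0.3 | 0.5 | 7.0 | 63% | −3.0 | 17% |
| 0.5 | 0.3 | 7.0 | 54% | −3.0 | 15% |
| 0.5 | 0.5 | 5.0 | 36% | −5.0 | 36% |

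By the formula, the sign of the bias reverses if the arm lowers satisfaction.

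**3. Omitting stoma.** Assume that 10% or 20% of patients have a stoma, that it lowers QoL by 5 or 10 points, and that the arms are balanced on it by stratification. Simulated type I error was 4.4% to 5.2% without stoma in the model and 4.8% to 5.3% with it. The Monte Carlo standard error at 4,000 replicates is √(0.05 × 0.95/4,000) = 0.34 percentage points, so these are hardly distinguishable from 5%.

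**4. If baseline QoL were entered only when the arms differ at p < 0.05** (ρ = 0.5, 8,000 replicates). It would enter in about 5% of trials. Power was 83.6%, against 91.5% when baseline is always adjusted for, and type I error was 4.2% against 4.8%. Such a rule would give up most of the gain in power without inflating false positives.

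**The case against.** The strongest reply is that the sentence is loose drafting. It lists what the arms will be compared on, and comparing them on cost and QoL is the primary objective. Read literally as an adjustment set, it would adjust QoL for QoL, which hardly anyone would intend. The list need not be exhaustive, cost and QoL are also measured at 1 month, and a journal article may leave the exact model to a fuller document.

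Much of this stands, and it rules out several stronger readings:

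- A reader might infer that covariates are selected because the arms differ on them. The text states no threshold and no such rule, and it refers adjustment to CONSORT. Check 4 above is therefore hypothetical.
- A reader might infer that the adjusted results will be biased. The text never says that the setting-level items enter an outcome model, so bias is conditional on that.
- A reader might infer that the trial loses its planned power. Unadjusted power at 68 per arm is still 82–83%, above the planned 80%.
- A reader might infer that omitting stoma materially distorts the inference. Check 3 shows a negligible effect.

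Leaving the model's details to an analysis plan would not be a fault in itself. What remains is that the article does publish a list, calls its members potential covariates, puts outcomes and post-allocation items in it, and then allows adjustment. A baseline reading of those items is strained. They are labelled by follow-up setting, and the cost definition that follows them includes GP visits, work-up of suspected relapse and treatment of relapse. The CONSORT reference does not take them off the list.

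**Conclusion.** The point holds as a defect in what the article states. The covariate list confuses outcomes and post-randomisation items with baseline variables. If those items were adjusted for, the treatment difference would be biased, by 1.8 to 5.0 points against a 10-point target under the assumed values of d and r. If they are kept out, the remaining cost is forgone precision from not naming the 1-month value: about 82–83% power against 86–98% for assumed correlations of 0.3 to 0.7, and 92% at 0.5. Leaving out baseline QoL or stoma does not bias the randomised comparison, and naming stoma matters for consistency with the design more than for error rates. The correlations, the arm effect on satisfaction, and the stoma share and effect are all assumptions; the effect size, SD, alpha, dropout and total sample size come from the protocol.

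**What to change.** - Delete cost, patient satisfaction and QoL by follow-up setting from the covariate list and report them as outcomes. By the same principle, the cost item listed under patient factors can stay only if it is defined as a pre-randomisation value.
- State that only pre-randomisation variables may be adjusted for, whatever the univariable arm comparisons show.
- Estimate each QoL difference with the 1-month value of the same scale, Dukes's stage and stoma as pre-specified covariates. If QALYs are compared, add 1-month EQ-5D as a covariate.
- Other pre-randomisation prognostic variables, such as age, sex and comorbidity, may stay as covariates if pre-specified.

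The cost is a change of analysis wording. No new data are needed: the 1-month questionnaires are already scheduled, and Dukes's stage and stoma status are needed to randomise each patient.

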**Methods and Design:**

Patients undergoing surgery for colon cancer with histological grade Dukes's Stage A, B or C and below 75 years of age are eligible for inclusion. They will be randomized after surgery to follow-up at the surgical outpatient clinic (control group) or follow-up by the district GP (intervention group). Both study arms comply with the national NGICG guidelines. The primary endpoints will be quality of life (QoL) (measured by the EORTC QLQ C-30 and the EQ-5D instruments), serious clinical events (SCEs), and costs. The follow-up period will be two years after surgery, and quality of life will be measured every three months. SCEs and costs will be estimated prospectively. The sample size was 170 patients.

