### Objectives

#### Primary objective

We aim to compare quality of life and costs of follow-up among patients followed up by their local GP or at the surgical outpatient clinic. We hypothesize that patients followed up by their GP will experience similar or higher scores on quality of life measures and lower costs during follow-up.

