### Secondary outcome measures

#### Serious clinical events (SCEs)

Time to detection of recurrences and serious clinical events (SCEs) defined as: Colonoscopy-verified recurrence of cancer disease. Increase in CEA measurements shown by repeated measurements. Blood in stool detected by the Hemofec test. Unexplained abdominal pain. Unexplained weight loss of 5 kg during the last three months. Cancer-suspect lesions detected in rectal examination. Lymphandenopathy. Metastatic suspect lesions shown by chest x-ray or ultrasound of liver.

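### No single decisive primary endpoint is fixed: several quality-of-life scores, costs and (in the abstract only) serious clinical events are called primary, and every test is run at 0.05

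*Protocol article*

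**What the plan says.** **Which outcomes are primary.** The abstract (Methods and Design) opens its list with "The primary endpoints will be quality of life (QoL", specifies this as "measured by the EORTC QLQ C-30 and the EQ-5D instruments", and continues with "serious clinical events (SCEs), and costs". In the body, the primary objective reads: "We aim to compare quality of life and costs of follow-up among patients followed up by their local GP or at the surgical outpatient clinic". SCEs are the subject of the secondary objective and stand under the heading "Secondary outcome measures".

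**What quality of life means.** The primary outcome section describes the EQ-5D, with an index and a VAS, and then the other instrument: "EORTC QLQ C-30 incorporates nine multi-item scales", to which it adds six single-item scales. Measurement is at nine time points from month 1 (baseline) to month 24. No scale, time point or summary is singled out.

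**Error rate.** The Analysis section says: "For all tests we will use alpha = 0.05 level of significance".

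**Sample size.** The numerical calculation concerns Global QoL: "This moderate effect size equals an increase of 10 units on the Global QOL", with an SD of about 20, two-sided alpha 0.05, beta 0.2 and 20% dropout, giving 170 patients. One further sentence says that EQ-5D calculations led to similar results, without figures. There is none for costs or SCEs.

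**Economic analysis.** Both the Economic analysis and the Analysis sections prescribe cost-minimization if no difference in health outcomes or quality of life emerges, and cost-utility if a quality-of-life difference is found. The Analysis section adds overall survival as a second trigger for cost-utility.

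**The concern.** Three parts of the article give different answers to the question of what is primary, and none reduces quality of life to one variable. Someone reading the results could not tell which comparison was meant to carry the conclusion.

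This can mislead in two directions. A chance benefit on one subscale could be presented as a primary finding. Equally, an absence of difference could be read off whichever scale or visit happens to show none. The primary objective predicts similar or higher quality of life under GP follow-up, so either reading would look like support for it.

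The economic evaluation inherits the problem. Costs belong to the primary objective, yet the form of the economic analysis depends on a quality-of-life difference whose measure is undefined, so it could be settled after the data are seen.

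**Working it through.** **1. The plan's own sample size.** Inputs from the Sample size section: difference 10, SD 20, two-sided alpha 0.05, power 80%, dropout 20%. A 1:1 ratio is assumed, as the article states none.

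- Per arm: n = 2 × (1.960 + 0.842)² × 20² / 10² = 62.8, so 63; the t-test version gives 64.
- Total with dropout: 126 / 0.8 = 157.5, so 158; with the t-test, 128 / 0.8 = 160.
- Stated: 170. The figure is not reproduced from the stated inputs, but the gap is on the safe side.
- Power of 170: 170 × 0.8 = 136, or 68 per arm. The standard error is 20 × √(2/68) = 3.43; 10 / 3.43 − 1.96 = 0.96; power is about 83%.

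The planned size therefore supports one Global QoL comparison at 0.05.

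**2. Counting what is labelled primary.**

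| Place | Called primary |
|---|---|
| Abstract | QLQ-C30, EQ-5D, SCEs, costs |
| Primary objective | Quality of life, costs |
| Primary outcome section | 9 + 6 = 15 QLQ-C30 scales, EQ-5D index, EQ VAS (17 scores) |
| Sample size, with inputs | Global QoL |

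**3. Familywise error at 0.05 per test.** Under independence it is 1 − 0.95^k. The correlated values come from simulating equally correlated normal test statistics. The correlations are assumptions; the article gives none.

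| k | Independent | Correlation 0.3 | 0.7 | 0.8 |
|---|---|---|---|---|
| 2 | 9.8% | 9.5% | 8.3% | 7.8% |
| 3 | 14.3% | 13.7% | 10.9% | 9.7% |
| 4 | 18.5% | 17.2% | 13.1% | 11.4% |
| 17 | 58.2% | 49% | 27% | 21% |

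k = 2 to 4 corresponds to one comparison for each outcome on the lists in the abstract and the primary objective. k = 17 corresponds to each quality-of-life score compared once.

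**4. The price of keeping several primaries.** This applies Bonferroni to the same Global QoL effect (10/20, 80% power, 20% dropout), as an illustration only.

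| Co-primaries | Alpha each | Total needed | Power with 170 |
|---|---|---|---|
| 1 | 0.05 | 158–160 | 83% |
| 2 | 0.025 | 193 | 75% |
| 3 | 0.0167 | 210 | 70% |
| 4 | 0.0125 | 225 | 66% |

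The planned size fits one primary test but not two or more with the error controlled in this way.

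**The case against.** The strongest reply is that this is a condensed article. A multiplicity rule, the longitudinal model and the handling of secondary scales are commonly left to a fuller document, and the 0.05 sentence sits beside rules for printing p-values, so it may only state a nominal reporting level. Costs are to be presented as incremental cost-effectiveness ratios, which is largely estimation already, and mean differences come with 95% confidence intervals. Much of this stands: absent modelling detail is no fault here, and no formal procedure for the secondary scales is required. It does not remove the contradiction over SCEs within the published text, nor supply the lead variable that the primary outcome section omits.

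Four stronger readings are tempting and are not supported:

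- **That the sample size rests on Global QoL alone.** The article also asserts an EQ-5D calculation. What is true is that only Global QoL has inputs.
- **That the stated error and power apply to nothing.** They apply to a Global QoL comparison; the text simply does not make that comparison decisive.
- **That a false positive is almost certain.** This takes 17 scores at 8 post-baseline visits, or 136 tests (1 − 0.95^136 = 99.9% if independent). The article says when data are collected, not that every scale is tested at every visit. One longitudinal comparison per scale is equally compatible with it.
- **That failing to reproduce 170 means too few patients.** The recomputed need is 158–160, below 170.

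**Conclusion.** The point holds in this form. The article labels several outcomes primary, contradicts itself on whether SCEs are among them, names no decisive scale, time point or summary for quality of life, and applies 0.05 to every test. The stated 5% error and 80% power cover a single Global QoL comparison but not the set called primary.

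The size of the excess depends on a number of tests that the article does not give. It is about 8–19% for two to four co-primaries, from two tests correlated at 0.8 to four independent tests. For 17 scores compared once it is about 27–49% at correlations of 0.7–0.3, and 58% if independent. Testing each scale at each visit would push it higher, but that is not stated. The choice between cost-minimization and cost-utility has no defined trigger on any of these readings.

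**What to change.** - Name the QLQ-C30 Global health status/QoL scale as the sole primary endpoint, since the worked calculation already uses it. Fix one contrast in advance, such as the mean GP-minus-hospital difference over months 3–24 from a repeated-measures model.
- Label the other QLQ-C30 scales, the EQ-5D index and the EQ VAS as secondary, reported with 95% confidence intervals. Make costs the economic endpoint, reported by estimation.
- Correct the abstract so that SCEs are secondary, as in the body.
- Restrict the confirmatory 0.05 test to the one primary contrast.
- State which quality-of-life result decides the type of economic analysis, and use the same triggers in the Economic analysis and Analysis sections.

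The cost is wording only, and 170 patients remain enough for a 10-unit difference at SD 20 under 1:1 allocation. The downside is that an isolated significant subscale can no longer be claimed as confirmatory. If the sponsor prefers several co-primaries, the error must be shared among them and the sample size revisited.
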